#### *6.7.7.13 Breaking the Randomization Code*

---

The AOSNA Methods Core is responsible for randomization assignment. The sites will be provided with the un-blinding information in case of emergency. In the event of an emergency, the principal investigator at the site will make the decision regarding the un-blinding. The investigator should not open the investigational product assignment blind unless knowledge of the subject's treatment is required for the subject's clinical care and safety. Documentation of breaking the blind should be recorded with the reason, date and time the blind was broken and the names of the personnel involved. The reason for un-blinding will be submitted to Sponsor/CRO within 24 hours and to IRB/REB/Ethical Committee per their regulations.

#### *6.7.7.14 Storage*

---

Investigational product/placebo must be stored in a secure, locked cabinet with limited access. Neither the Investigator nor any member of the study staff will distribute any of the Investigational Drug to any person not participating in this study. The drug should be stored at a temperature between 15°-30°C (59°-86°F) and protected from bright light.

The Investigational Drug will be dispensed at the discretion and by the direction of the Investigator in accordance with the conditions specified in this Protocol. It is the Investigator's responsibility to ensure that accurate records of Investigational drug issuance and return are maintained.

It is expected that the site staff will maintain temperature logs in the investigational product storage area, recording the temperature at least once each working day.

#### *6.7.7.15 Investigational Drug Accountability*

---

The investigational site will maintain an inventory of the Investigational Drug. This will include:

- Name of person designated as responsible for the inventory of the investigational product
- Amount received including date, and lot number
- Amount currently in inventory
- Amounts dispensed to each subject, identified by subject initials and a unique subject study number
- Amount destroyed, if applicable – this should not occur without prior notification to Sponsor/CRO
- Non-study disposition (e.g. wasted, broken)
- Amount returned to Sponsor or designee, if applicable

Sponsor, or its designee, will provide forms to facilitate investigational product inventory control. All investigational product accountability forms and treatment logs must be retained in the site's regulatory binder. These records must be available for inspection by the Sponsor, its designees or by regulatory agencies at any time.

Investigational Drug shipment to sites will be accompanied by a Drug Shipment Form which must be signed and dated upon receipt and copy sent back to the Sponsor/CRO. This form must be filed in the site regulatory binder.

#### *6.7.7.16 Assessment of Subject Compliance*

---

Compliance will be recorded by the Study Research Coordinator or Investigator during enrollment at 14-day post-enrollment and will be documented on the appropriate SW (Medication Compliance SW). Subjects must have 80% or greater compliance. The subject is considered compliant if he/she has taken at least 24 capsules.

Failure to comply will be considered a Protocol Violation and will be recorded on the Protocol Violation Form. Non-compliant subjects will remain in the study and will undergo the same study procedures as compliant subjects.

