## 6.7.2 Investigational Drug Dose and Administration

### 6.7.2.1 Dose

Subjects will receive a total of 28 doses of Investigational Drug, administered twice a day, for a total of 14 days. The riluzole group will receive riluzole in a dose of 100 mg at 0 hours and 12 hours (doses 1 and 2) followed by 50 mg doses every 12 hours for the next 13 days (doses 3 - 28). The control group will receive placebo capsules in a dose of two capsules at 0 hours and 12 hours (doses 1 and 2) followed by one capsule every 12 hours for the next 13 days (doses 3 to 28).

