### *6.7.2.2 Administration of Study Drug*

---

The first two doses of study drug must each be given according to the Protocol schedule (i.e. at 0 hours and 12 hours). The third dose can be administered to align with the standard hospital medication administration schedule. If the next standard hospital medication administration time falls 4 or more hours after the second dose, the third dose should be administered at that time. If the next standard hospital medication administration time falls less than 4 hours after the second dose, that time shall be skipped and the third dose should be administered at the second standard hospital medication administration time. Doses 4 through 28 should be administered every 12 hours.

For example, a hospital's standard medication administration times are 09:00 (9:00 AM) and 21:00 (9:00 PM).

- Patient A's first dose is given at 03:30 (3:30 AM) and the second dose is given at 15:30 (3:30 PM). More than 4 hours elapse before the next standard medication administration time, so the third dose is given at 21:00 (9:00 PM), the fourth dose at 09:00 (9:00 AM) and afterwards every 12 hours.
- Alternatively, Patient B's first dose is given at 06:00 (6:00 AM) and the second dose is given at 18:00 (6:00 PM). The standard medication administration time (21:00) is only 3 hours after the second dose, so the third dose is given at 09:00 (9:00 AM) the next day, the fourth dose at 21:00 (9:00 PM) and afterwards every 12 hours.

For subjects who are unable to receive oral medications, the filler from each capsule will be mixed with 3 mL of water and will be delivered via nasogastric tube.

The investigational drug should be taken at least an hour before, or two hours after, a meal to avoid a food-related decrease in bioavailability. If the subject is on a continuous feeding schedule via nasogastric tube, it is recommended that feeding is stopped to accommodate the above drug administration schedule, as long this is not clinically contraindicated. If there is a clinical contraindication to stop feeding via nasogastric tube, the drug should be administered without interruption of continuous feeding.

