### **Criteria to discontinue Investigational Drug due to possible drug induced liver injury**

- ALT or AST >8xULN
- ALT or AST >3xULN and (TBL >2xULN or International Normalized Ratio (INR) >1.5)
- ALT or AST >3xULN with the appearance of fatigue, nausea, vomiting, right upper quadrant pain or tenderness, fever, rash, and/or eosinophilia (>5%)

If the patient reaches the above criteria to discontinue investigational medication the blind will not be broken, except in the case of patient safety concerns. All trial subjects showing possible investigational drug-induced liver injury will be followed until all abnormalities return to normal or to the baseline state, until declared clinically insignificant or until the status is declared as unresolved. However, no subjects will be followed-up beyond the final study follow-up visit.

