### *7.13.4 Per-protocol Population*

---

The Per-protocol population (PP) population is a subset of CC population and it includes all enrolled patients entirely consistent with the Protocol and who received at least 80% of study-directed treatment and had 180 days of follow-up. Any visits where Protocol violations occurred will be reviewed for possible exclusion from PP population.

The patients with major Protocol violations will be tabulated by violation type and affected visit(s), where applicable. All Protocol violations will be listed.

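### The flat 24-of-30-capsule compliance rule records a drug stop required on a day-3 or day-7 liver result as a Protocol Violation, and classes as compliant a subject who did not receive the specified loading doses

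*Protocol*

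**What the plan says.** Section 6.7.2.1 sets the course: "Subjects will receive a total of 28 doses of Investigational Drug, administered twice a day, for a total of 14 days". The control arm takes "placebo capsules in a dose of two capsules at 0 hours and 12 hours (doses 1 and 2") and a single capsule at each of the remaining 26 doses. The riluzole arm takes 100 mg at doses 1 and 2 and 50 mg afterwards. Section 6.7.2.2 makes the start of the course mandatory: "The first two doses of study drug must each be given according to the Protocol schedule (i.e. at 0 hours and 12 hours").

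Section 6.7.7.16 asks for at least 80% compliance and turns that into a count: "The subject is considered compliant if he/she has taken at least 24 capsules". It continues: "Failure to comply will be considered a Protocol Violation and will be recorded on the Protocol Violation Form". No exception is given. Non-compliant subjects remain in the study.

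Section 6.7.2.3 schedules liver chemistry on days 3, 7 and 14 and lists three criteria for discontinuing drug. The first is "ALT or AST >8xULN"; the other two combine a rise above 3 times the upper limit of normal (ULN) with raised bilirubin or INR, or with symptoms.

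The per-protocol set in 7.13.4 takes subjects whose conduct fully matched the protocol and who "received at least 80% of study-directed treatment and had 180 days of follow-up". Section 13.4 defines a violation as a significant departure from the protocol. Section 6.7.7.12 instructs hospital staff to give a single capsule at each 12-hourly dose, with a pointer to 6.7.2 for further explanation.

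**The concern.** A compliance rule should separate subjects who followed the regimen from those who did not. This one can fail in two ways.

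First, a stop that 6.7.2.3 requires leaves the subject short of 24 capsules if it follows the day-3 or day-7 test. The site must then file correct conduct as a violation. Under 13.4 that means immediate notice to the sponsor and reporting to the IRB as required; under 7.13.4 it means listing with the other violations. The protocol states in 6.7.2.3 that riluzole can raise aminotransferases, so the mislabelled subjects may not be spread evenly over the arms.

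Second, the total count cannot show whether doses 1 and 2 were given as specified. Single-capsule dosing throughout corresponds to the Phase I schedule in 5.2.6 (50 mg every 12 hours, 28 doses), not to this trial's regimen, and the staff instruction in 6.7.7.12, read alone, produces exactly that pattern.

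**Working it through.** **The plan's own figure.** Capsules in a full course (6.7.2.1): 2 × 2 + 26 × 1 = 30. Then 0.80 × 30 = 24, so the threshold reproduces exactly. Counting doses instead would give 0.80 × 28 = 22.4, so the base is capsules. One assumption: capsule strength is not stated for the riluzole arm, but blinding implies the same capsule counts as placebo.

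**When the 24th capsule is due.** Doses 1 and 2 supply 4 capsules, so the 24th comes at dose 22. Let d be the time of dose 3 in hours after dose 1. Section 6.7.2.2 allows dose 3 from 4 hours after dose 2 (d = 16); its second worked example gives d = 27; the plain schedule gives d = 24. Dose 22 falls at d + 19 × 12 = d + 228, that is 244, 252 or 255 hours, about day 10.2 to 10.6.

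**Capsules taken by a stop at hour t.** Doses taken = 3 + floor((t − d)/12); capsules = doses + 2.

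| Stop | t (hours after dose 1) | Capsules | Share of 30 |
|---|---|---|---|
| Day-3 draw, whole window | 48 to 84 | 6 to 10 | 20% to 33% |
| Day 7 | 168 | 16 to 17 | 53% to 57% |
| Day 8, end of the day-7 window | 192 to just under 216 | 18 to 21 | 60% to 70% |
| 72-hour repeat of a nominal day-7 draw | 240 | 22 to 23 | 73% to 77% |
| 72-hour repeat of a day-8 draw | 264 | 24 to 25 | 80% to 83% |

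Example: t = 168, d = 24 gives 3 + floor(144/12) = 15 doses and 17 capsules. The day-3 range arises because that visit is timed from injury (72 ± 12 hours) and dose 1 may come up to 12 hours after injury.

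A stop made on the day-3 or day-7 result itself therefore leaves 6 to 21 capsules and always fails. Only a stop delayed to a late repeat of a day-8 draw reaches 24.

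**The other direction.**
- One capsule at each of 28 doses: 28/30 = 93%; on the 50 mg assumption, 1400/1500 mg = 93%.
- Dose 2 omitted, the rest as planned: 28/30 = 93%.
- Doses 1 and 2 both omitted: 26/30 = 87%.

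All three are at or above 24 and are classed compliant.

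**Side by side.** Section 6.7.2.3 requires the stop; 6.7.7.16 calls the resulting count a violation; 13.4 reserves that term for departures from the protocol. Section 6.7.2.2 makes doses 1 and 2 mandatory; 6.7.7.16 gives them no weight beyond their capsules; 6.7.7.12 describes single-capsule dosing. These sections must be reconciled.

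**The case against.** Several points on the other side are sound.

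- A reader might infer that the per-protocol analysis keeps subjects who never had the loading doses. Section 7.13.4 does not support that. Besides the 80% exposure rule it demands conduct fully in line with the protocol, and it reviews violations for possible exclusion. A subject without the specified doses 1 and 2 may already be removed there. What remains is that 6.7.7.16 calls the same subject compliant.
- A reader might infer that every liver stop fails the count. The last row of the table shows an exception.
- A reader might infer that stops will be more frequent on riluzole and that the per-protocol comparison is therefore biased. The protocol gives no stopping rate. Table 6 shows abnormal ALT in 29% against 14% and abnormal AST in 23% against 19%, but for any abnormality in ALS trials. In Phase I (5.2.6.2) the reported severe values were ALT 6 and AST 5.5 times ULN, below the criterion of more than 8 times, and elevations became more frequent in the second week. Phase I does not say how many patients would have met the two combined criteria. An imbalance is possible, not established.
- Leaving under-exposed subjects out of a per-protocol set is customary. Keeping them changes the question that set answers; it does not correct an error.
- Omitting dose 1 outright is an unlikely route, since 6.7.1 ties enrolment to receipt of the first dose.
- Section 13.4 could be read as exempting a required stop. But 6.7.7.16 defines compliance by the count alone, and a site following it as written has no basis for withholding the violation form.

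**Conclusion.** The point holds as a classification fault with two parts. The firmer part is the label: a stop required by 6.7.2.3 on a day-3 or day-7 result leaves about 6 to 21 of 30 capsules and is recorded as a Protocol Violation, contrary to 13.4. The second part is that the rule passes subjects without the specified loading doses, at 93% or 87%, while the staff instruction in 6.7.7.12 makes the single-capsule error possible.

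The figures rest on on-schedule dosing, dose 3 at 16 to 27 hours, equal capsule counts in both arms, and a stop made when the result is acted on within the visit window. Loss from the per-protocol set further assumes that the 80% in 7.13.4 is measured against the full course. The number of subjects affected and the balance between arms are unknown. Primary efficacy is analysed by intention to treat (7.13.5), so the main conclusion of the trial is unaffected; what suffers is the violation record, the compliance classification and possibly per-protocol membership. It should be corrected, but it does not threaten the trial.

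**What to change.** 1. In 6.7.7.16, record a stop made under 6.7.2.3 as a protocol-directed discontinuation, not as a Protocol Violation.
2. In 6.7.7.16 and 7.13.4, assess receipt of doses 1 and 2 separately from the total count when classifying compliance and per-protocol membership.
3. Reconcile 6.7.2, 6.7.7.12, 6.7.7.16, 7.13.4 and 13.4, so that the staff instruction, the dosing section, the compliance rule and the definition of a violation agree. No dose or stopping rule is proposed here.
4. State whether protocol-directed stoppers remain in the per-protocol set. This is the sponsor's choice: including them admits shortened exposure, while excluding them risks a loss that differs by arm. If they are excluded, a sensitivity analysis with them included would show any differential exclusion.

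The cost is a few sentences. The dose records are already collected on the dispensing and Medication Compliance worksheets, so no new data are needed.

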#### *6.7.8 Medical and Surgical Care*

---

Medical care for the acute SCI, including blood pressure management, will follow established standards of care [15]. Decompressive surgery for SCI in the acute setting post-injury will be performed as per standard of care at the treating institution. Wherever possible, however, surgical decompression of the spinal cord will be undertaken within 24 hours of injury. The surgical approach, medical devices and bone grafts/bone graft substitutes used will be at the surgeon's discretion.

### *6.7.9 Post-surgical Rehabilitation and Occupational Therapy*

---

Post-treatment rehabilitation and occupational therapy procedures will be per standard of care at the investigational site. The number of hours of rehabilitation and occupational therapy will be recorded.

### *6.7.10 Clinical Laboratory Procedures*

---

Blood draws for the clinical laboratory examinations will be taken at screening and days 3, 7 and 14 after the treatment initiation (Table 2).

**Table 2 Clinical lab blood tests**

| Examination                               | Screening | 72 hours $\pm$ 12 hours | 7 $\pm$ 1 days post treatment | 14 + 2 days post treatment |
|-------------------------------------------|-----------|-------------------------|-------------------------------|----------------------------|
| AST (SGOT)                                | X         | X                       | X                             | X                          |
| ALT (SGPT)                                | X         | X                       | X                             | X                          |
| ALP                                       | X         | X                       | X                             | X                          |
| GGT                                       | X         | X                       | X                             | X                          |
| Bilirubin                                 | X         | X                       | X                             | X                          |
| INR                                       | X         | X                       | X                             | X                          |
| Creatinine (mg/dL)                        | X         | X                       | X                             | X                          |
| Red Blood Cell (RBC)                      | X         | X                       | X                             | X                          |
| White Blood Cell (WBC)                    | X         | X                       | X                             | X                          |
| Hemoglobin (Hbg)                          | X         | X                       | X                             | X                          |
| Hematocrit (Hct)                          | X         | X                       | X                             | X                          |
| Neutrophils                               | X         | X                       | X                             | X                          |
| Immature Polys                            | X         | X                       | X                             | X                          |
| Lymphocytes                               | X         | X                       | X                             | X                          |
| Monocytes                                 | X         | X                       | X                             | X                          |
| Eosinophils                               | X         | X                       | X                             | X                          |
| Basophils                                 | X         | X                       | X                             | X                          |
| Platelet Count                            | X         | X                       | X                             | X                          |
| Mean Cell Hemoglobin Concentration (MCHC) | X         | X                       | X                             | X                          |
| Reticulocyte                              | X         | X                       | X                             | X                          |
| ANC                                       | X         | X                       | X                             | X                          |

## 6.8 Subjects Completion and Disposition

### 6.8.1 Screen Failure

Screen failure is defined as a subject who has signed the ICD but does not meet the eligibility criteria, was not enrolled by the Investigator for any reason or withdraws consent for any reason

prior to enrollment. A subject may be considered a screen failure any time prior to enrollment. Screening SWs will be completed for all screen failures, and the reason for failure will be indicated.

### *6.8.2 Enrolled Subject*

---

A subject is considered to be enrolled into the trial when Randomization is completed.

### *6.8.3 Withdrawn (Discontinued) Subject*

---

Reasonable efforts to keep each subject in the study will be made and must be documented by the Investigator. A subject will be withdrawn from the study for any of the following reasons:

- In rare cases subject may be enrolled prior to receiving all screening laboratory tests. If the results show clinically significant abnormalities, the subject may be discontinued.
- Subject voluntarily withdraws consent after enrollment and terminates participation.
- The Investigator withdraws the subject. If this decision is made for safety reasons or non-compliance with the study Protocol or procedures the Sponsor/CRO will be notified immediately.
- The Investigator or the Sponsor stops the study or stops the patient's participation for medical, safety, regulatory or other reasons consistent with applicable laws, regulations and Good Clinical Practice (GCP).

For each case, detailed information will be obtained explaining circumstances leading to the withdrawal. This will be recorded on the Subject Withdrawal Form. Investigational Drug assigned to the withdrawn subject shall not be assigned to another subject. The remaining study medication for the withdrawn subject will be obtained from the subject and kept at the site to be processed at the end of the study according to the disposal or return instructions.

For safety reasons, a subject who withdraws from the study for any reason before completion of the dose regimen and the last scheduled lab test will be assessed for safety evaluation purposes. This shall occur within 30 days of the last dose of the Investigational Drug.

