### 6.7.1 Screening and Enrollment

---

Screening and enrollment is schematically shown in Figure 1.

Subjects with acute SCI who present to a participating center within 12 hours of injury will be screened for inclusion. Prior to any screening procedures, subjects will sign the ICD. If the subject meets all of the eligibility criteria, he/she will be randomized and enrolled into the study. The randomization will occur as soon as possible after the eligibility has been determined and the first dose of Investigational Drug will be administered not later than 12 hours from the time of injury. Given the nature of this study and very short period available for the screening, in some rare instances a patient may be enrolled and receive the Investigational Drug prior to receipt of all screening laboratory results. In such rare cases, a clinically significant abnormal value for any of the tests may result in the discontinuation of the patient.

The subject will be considered enrolled into the study when the randomization occurs, and the first dose of study medication is administered.

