#### *7.13.1 Intention-to-Treat*

Consenting subjects who qualify, are randomized to a study arm and receive at least one dose of study medication (i.e. enrolled subjects) will be included in the Intent-To-Treat (ITT) analytic

sample primary analysis population, regardless of the actual treatment received. Screen failures will be recorded on the Screening SW and will not be included in the ITT group. Values for the subjects who do not have the 180 day end point will be imputed to create a complete ITT population.

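### Section 6.8.3 does not separate stopping drug from leaving the study, and the primary ITT set can omit randomized subjects who were undosed or judged not to qualify

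*Protocol*

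**What the plan says.** **Withdrawal (6.8.3).** The section heading treats withdrawn and discontinued as the same thing, and the list opens with "A subject will be withdrawn from the study for any of the following reasons". One listed reason is a screening result that arrives after enrollment: "If the results show clinically significant abnormalities, the subject may be discontinued". Another is withdrawal by the investigator, where "If this decision is made for safety reasons or non-compliance with the study Protocol or procedures the Sponsor/CRO will be notified immediately". Subjects who leave before completing the regimen and the last scheduled lab test get a safety assessment no later than 30 days after their last dose. No 180-day examination is asked for.

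**Late labs (6.7.1).** In rare cases "a patient may be enrolled and receive the Investigational Drug prior to receipt of all screening laboratory results", and then "a clinically significant abnormal value for any of the tests may result in the discontinuation of the patient". This does not say whether the drug or study participation stops.

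**Non-compliance (6.7.7.16).** Failing the drug-compliance standard is a protocol violation, but "Non-compliant subjects will remain in the study and will undergo the same study procedures as compliant subjects".

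**Enrollment.** Section 6.8.2 says "A subject is considered to be enrolled into the trial when Randomization is completed", and 6.7.5 agrees. Section 6.7.1 also requires that the first dose has been given.

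**Primary analysis set (7.13.1, 7.13.5).** ITT is "Consenting subjects who qualify, are randomized to a study arm and receive at least one dose of study medication", with a parenthesis equating these to the enrolled subjects. Missing 180-day values in this set are imputed. It is the primary efficacy population.

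**The concern.** Dosing lasts 14 days and the primary endpoint is read at day 180, so about 166 days of follow-up (180 − 14) come after the last planned dose. A subject who stops drug early can still have the motor score measured at day 180. If stopping drug is handled as leaving the study, that score is not collected, and an assumption takes its place in the primary analysis. Section 7 leaves the handling of missing values to the SAP, but no SAP can recover an examination that was never done.

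The second issue is who is counted. A set defined by all randomized subjects keeps the comparison that randomization created. Adding conditions met or judged after randomization (receiving a dose, being found to qualify once labs return) allows subjects to be removed afterwards. Because the protocol defines enrollment in two ways, two analysts could build different primary sets and each point to text in support.

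**Working it through.** **1. The plan's own sample size.** Inputs (synopsis, 7.9, Table 4): difference 9, SD 24.08, one-sided alpha 0.025, power 90%, one interim look at 60%, O'Brien-Fleming-type efficacy boundary, gamma(−1) binding futility boundary.

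- Alpha spent at the interim: 2 × [1 − Φ(z₀.₉₈₇₅ / √0.6)] = 0.0038
- Beta spent at the interim: 0.10 × (1 − e^0.6)/(1 − e^1) = 0.0478
- Drift needed for 90% power under these boundaries: θ = 3.321
- N = 4 × (θ × SD / difference)² = 4 × (3.321 × 24.08 / 9)² = 315.8, against 316 stated
- Attrition: 316 / 0.9 = 351.1, against 351 stated; allowance 351 − 316 = 35 subjects

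The computed stopping probabilities also match Table 5. The sample size is sound, and the point concerns conduct and population rules.

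**2. What happens to each kind of randomized subject if the text is followed.**

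| Subject | Governing text | 180-day score | In primary set? |
|---|---|---|---|
| Stops drug on the liver criteria | 6.7.2.3: drug stopped, abnormality followed | Collected | Yes |
| Misses the drug-compliance standard | 6.7.7.16 keeps the subject in; 6.8.3 permits withdrawal | Depends on which section the site applies | Yes, imputed if withdrawn |
| Withdrawn by the investigator for safety | 6.8.3 | Not asked for | Yes, imputed |
| Dosed before labs return, then found ineligible | 6.7.1, 6.8.3, 7.13.1 | Not asked for if withdrawn | Unclear: enrolled under every definition, but may not qualify |
| Randomized, never dosed | 6.8.2 and 6.7.5: enrolled; 6.7.1 and 7.13.1: not | Not settled | No |

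The last two rows show that the parenthesis in 7.13.1 cannot hold as written. An undosed randomized subject is enrolled under 6.8.2 but outside ITT. A dosed subject found ineligible is enrolled under 6.7.1 but may fail the qualifying condition.

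**3. Effect on power, for scale only.** The documents give no withdrawal rate, so the share of the 351 without an observed 180-day score is an assumption. With the planned boundaries and θ = (9 / 24.08) × √(N/4), counting observed subjects only:

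| Assumed share missing | Observed N | Power |
|---|---|---|
| 0% | 351 | 92.7% |
| 5% | 333 | 91.4% |
| 10% (planned) | 316 | 90.0% |
| 15% | 298 | 88.3% |
| 20% | 281 | 86.4% |
| 25% | 263 | 84.2% |

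**4. Effect on bias.** The shift in the arm difference is w_R × g_R − w_P × g_P, where w is the share withdrawn in each arm and g the mean gap between the imputed and the unobserved true score. The documents give neither w nor g, and g depends on an imputation method left to the SAP. The shift cannot be calculated from what is available.

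**The case against.** Much of the case on the other side stands.

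- **The conflict with 6.7.7.16 is narrow.** A reader might infer that all of 6.8.3 contradicts it, or that 6.8.3 orders non-compliant subjects out. Neither is supported. Section 6.7.7.16 is about drug compliance only. The item in 6.8.3 covers a withdrawal the investigator has decided on and then requires notification, so it permits and does not command. The overlap exists because 6.7.7.16 makes drug non-compliance a protocol violation. The specific rule could be read as governing, but the text does not say so.
- **Liver findings do not establish unequal withdrawal.** Table 6 shows abnormal ALT in 29% on riluzole and 14% on placebo, and a reader might infer unequal study withdrawal. That does not follow. Section 6.7.2.3 stops the drug on its own criteria and continues follow-up, Table 6 comes from ALS trials, and 5.2.3 says threefold ALT rises were reported only after several months of treatment.
- **Two routes are unlikely to differ by arm.** Screening labs reflect pre-dose status, failure to receive a first dose cannot be caused by the drug, and site staff are blinded. Late-lab cases are called rare, and that item says only that discontinuation may follow. Investigator withdrawal for safety after dosing is the route that could plausibly differ.
- **Withdrawal does not mean removal from ITT.** Dosed, qualifying subjects who are withdrawn stay in the set; what is lost is their observed score.
- **Sites are told to try to retain subjects.** Section 6.8.3 says so, but it asks for no 180-day visit once a subject is withdrawn.

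These limits reduce the expected harm. They do not resolve the mixing of drug and study discontinuation, the two enrollment definitions or the extra conditions on ITT.

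**Conclusion.** The point holds as a defect of wording with consequences for the primary analysis. Followed as written, 6.8.3 loses 180-day scores that could have been measured, 7.13.1 imputes them, and some randomized subjects can be left out of the primary test. The inconsistency with 6.7.7.16 is real for non-compliance only.

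Confidence is high on the text and low on the size. No withdrawal rate, count of undosed subjects or imputation gap is given, so the bias could be negligible and no figure in motor-score points is warranted. Power is secondary: the 10% allowance covers about 35 losses, and even an assumed 20% without observed data leaves 86.4%. Avoidable missing outcomes and exclusion after randomization are the reasons to act.

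**What to change.** - **6.8.3:** define discontinuing investigational drug and withdrawing from the study as separate events. Ask every randomized subject to attend the scheduled 180-day ISNCSCI visit unless consent is withdrawn, the subject dies or the study closes. State in 6.7.1 and 6.8.3 which event a late abnormal lab result leads to.
- **6.8.3 and 6.7.7.16:** reconcile them so that a site has one instruction on study participation for non-compliant subjects.
- **7.13.1:** define ITT as all randomized subjects, analyzed by assigned arm, without the qualifying and dosing conditions. The mITT set in 7.13.2 already requires a dose.
- **6.7.1, 6.7.5, 6.8.2 and 7.13.1:** use one definition of enrollment.

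The cost is a protocol amendment, some extra follow-up effort for subjects off drug, and slight dilution of the effect from including never-dosed subjects. The 180-day visit is already in Table 1 for every subject. The planned sample size and the drug-stopping criteria do not change.
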